**Figure 1 figure1:**
[figure not shown]
Intervention design. EMA: ecological momentary assessment; t: time point.

### Intervention

The underlying theory for this web-based intervention is based on the assumptions of the Integrated Behavioral Model. This model posits that the most important determinant of behavior is the intention to perform the behavior, informed by individuals’ attitudes, perceived norms, and personal agency [16]. Within this model, intention to perform a behavior is modified by four key factors: knowledge and skills, environmental constraints, the salience of the behavior to the individual, and the role of habits [16]. The Transtheoretical Model of Change [17] will also be used to determine each participant’s readiness to change their alcohol use to understand how the intervention impacts motivation to change*.* The intervention also follows the principles of brief interventions for substance use [18]. Additionally, the intervention is based on the outcomes of interactive focus group workshops that were run by the research team with women aged 40-65 years.

### The Integrated Behavioral Model

Initially, participants will be surveyed on their alcohol use and provided with feedback on their current consumption, in line with brief intervention practice. Following this, participants will *set goals* around their intentions to reduce their alcohol use over the period of the intervention in order to promote personal agency or self-efficacy. Participants will also be able to *track their alcohol use* throughout the intervention period to become more aware of their habits and behaviors. Participants will work through four *modules of content*, which will provide information aimed at changing participants’ attitudes and perceived norms. This will include the following: (1) the Low-Risk Drinking module, which will provide evidence on the harms of alcohol use and information on what a standard drink is; (2) the Mindful Drinking module, which will provide information about drinking motives and provide participants with skills to both learn to consume alcohol mindfully and to apply the broader techniques of mindfulness to their lives to reduce the common antecedents of alcohol use (such as stress); (3) the Social Drinker module, which will explore the social influences of drinking, including facts about how people influence each other both consciously and unconsciously, encourage participants to reflect on where alcohol currently fits into their social lives, and help build participant’s skills to talk about their alcohol consumption with others; and (4) the Alcohol is Everywhere module, which will look at the broader factors that influence alcohol consumption, including information about the normativity of alcohol in Australian society and how alcohol availability and outlet density impact consumption, the ways in which the alcohol industry specifically targets women, how alcohol advertising impacts children, and the broader alcohol industry tactics used to promote their products. The overall aim of the content is to make participants more aware of their alcohol use and the impacts it has on their lives and on the lives of others, in order to produce attitudinal and normative changes, while building skills to cope with stress and increase self-efficacy for reducing consumption in social situations.

To improve participants’ knowledge and skills to reduce their alcohol use, and to remove environmental constraints, each module will have between 1 and 3 associated *challenges*. The challenges include, for example, an opportunity for participants to write a script for a conversation with a friend or family member on how to say no when offered alcohol, information on alternate activities participants can do to relax, and an opportunity to track how they engage in these activities over a 1-week period.

Participants will be sent reminders to complete their assessments, and upon completion of the assessment, will be redirected back to the intervention content. Participants can complete the intervention content in any order and will have the entire intervention period to access and work through all of the content.

At the conclusion of the trial, participant summaries will be developed and distributed to those participants who request one.

### Comparator

Participants in control group 1 will not be contacted again until the 8-week follow-up questionnaire. Participants in control group 2 (baseline and follow-up assessment plus EMA) will undertake the web-based repeated measures assessment of their alcohol consumption retrospectively twice a week. After they are recruited and randomized, these participants will be sent a link via text message to a web-based EMA. The assessment on Sunday at 12 PM will ask them about their drinking patterns over the weekend (ie, Thursday afternoon until Sunday morning), and the assessment on Thursday at 12 PM will ask about their drinking patterns during the week (ie, Sunday afternoon until Thursday morning). All participants in the control groups will be given access to the web-based intervention at the completion of the study.

### Outcomes

The primary outcomes include frequency of alcohol consumption, as well as alcohol intake per drinking occasion. The secondary outcomes are awareness of alcohol-related harms, willingness to change alcohol consumption, alcohol-related harm, current health status, mental health, and social support or loneliness.

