**Methods:**

The study is a 3-arm randomized controlled trial with a web-based intervention plus ecological momentary assessment (EMA) group compared to an EMA-only and a pre-post only control group. The study is aimed at middle-aged women, defined as women aged between 40 and 65 years, who consume alcohol at least weekly or who have consumed 4 or more drinks on 1 occasion in the last month. The intervention aims to reduce alcohol consumption through 4 modules that provide information on the health impacts of alcohol, mindfulness, social influences, and alcohol marketing. Intervention participants will also fill out biweekly EMA assessments. The comparators are EMA-only and pre-post control only. The primary outcome is alcohol consumption at 8 weeks compared between groups. Secondary outcomes are awareness of alcohol-related harms, readiness to change alcohol consumption, health status, mental health, and social support.

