There is a specific need for interventions designed by, and targeted at, middle-aged women for several reasons. Firstly, men and women have different patterns of alcohol use and different motives for consumption [3,8,9]. For example, women are lighter drinkers than men, and use alcohol to experience respite from their traditional female domestic and caring responsibilities. Further, most web-based interventions that are female-centric have been aimed at pregnant women or those of childbearing age, with the content heavily tailored to these specific groups and a particular focus on the harms of alcohol to unborn babies [10,11]. Lastly, it has been shown that tailoring interventions using co-design with a target population is particularly efficacious in ensuring the effectiveness of an intervention or program [12,13]; thus, an intervention designed by and for middle-aged women is likely to have amplified effectiveness.

To our knowledge, there are no web-based interventions targeted specifically at middle-aged women that have been documented in the literature. Our study aims to fill this gap by developing and testing the effectiveness of a web-based intervention in reducing alcohol consumption among women aged 40-65 years. The primary aim of this study is to test the effectiveness of a 3-arm web-based intervention in reducing both the frequency of alcohol consumption as well as the alcohol intake per occasion among middle-aged women. Secondary aims include testing the effectiveness of the intervention in increasing awareness of the long- and short-term harms associated with alcohol consumption, increasing motivation to reduce alcohol consumption, reducing alcohol-related harm, improving reported health status and mental health, and increasing social support. We will also test reactivity to the ecological momentary assessment (EMA) by comparing a control group with weekly assessment to a pre-post control group.

### Hypothesis 1

We hypothesize that by the end of the intervention period, participants in the web-based intervention group will report significantly lower alcohol consumption compared with participants in the pre-post control group (H1).

### Hypothesis 2

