##### Daily Alcohol Consumption (Baseline, EMA, and Follow-up)

Participants’ daily alcohol consumption will be measured using a drinking diary, where twice a week they will retrospectively report on the number of beverages they consumed each day (eg, “Thinking back over the last three days, how many standard drinks containing alcohol did you have on each day of the week?”)

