## Discussion

### Expected Outcomes

This paper describes the study protocol of a randomized controlled trial to assess the benefit of a targeted web-based intervention to reduce alcohol consumption among middle-aged women. Intervention with this group is imperative because their alcohol consumption has increased at a time when that of other groups has remained stable or declined [35]. The primary aim of the study is to test whether a web-based intervention can reduce alcohol consumption, increase awareness of alcohol-related harms, increase motivation to reduce alcohol consumption, increase social support and reported health status, and decrease alcohol-related harms, when compared to a no-intervention control group.

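### The primary outcome is stated in three ways, and one stated primary, intake per drinking occasion, has no value for a woman with no drinking occasion at follow-up

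*Protocol article*

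**What the plan says.** The protocol article describes what is primary at three levels.

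- **One outcome.** The abstract (Methods) says "The primary outcome is alcohol consumption at 8 weeks compared between groups". Hypothesis 1 predicts that intervention participants "will report significantly lower alcohol consumption compared with participants in the pre-post control group (H1"). Neither names a component.
- **Two outcomes.** In the Introduction the primary aim is "reducing both the frequency of alcohol consumption as well as the alcohol intake per occasion among middle-aged women". The Outcomes section agrees: "The primary outcomes include frequency of alcohol consumption, as well as alcohol intake per drinking occasion". The verb in that sentence leaves the list open, and the two outcomes are not ranked.
- **Six items.** The Discussion (Expected Outcomes) says "The primary aim of the study is to test whether a web-based intervention can reduce alcohol consumption, increase awareness of alcohol-related harms". It goes on to motivation, and then to "increase social support and reported health status, and decrease alcohol-related harms, when compared to a no-intervention control group".

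The Introduction treats the five items other than consumption as secondary. Its sentence opens "Secondary aims include testing the effectiveness of the intervention in increasing awareness of the long- and short-term harms associated with alcohol consumption" and continues with motivation, harm, health and social support. The Outcomes section lists matching secondary outcomes.

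Two instruments could yield the primary outcome, and both are labelled for baseline and follow-up: a typical-week question asked for each weekday, and a daily diary in which "twice a week they will retrospectively report on the number of beverages they consumed each day". The article does not say which one feeds the primary comparison.

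**The concern.** H1 is the hypothesis on which the trial will be judged, and the article does not fix what decides it. The two components can move apart. With invented figures, a woman who goes from 4 drinking days at 2 drinks (8 a week) to 3 days at 2.5 drinks (7.5 a week) improves on frequency and total but worsens on intake per occasion. If an arm behaves this way, the article does not say whether H1 is met. The wording in the Discussion would also let a gain in awareness or social support be presented as meeting the primary aim.

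The second problem is the choice of measure. Intake per drinking occasion is a ratio whose denominator is the behaviour the intervention is meant to reduce. A woman who stops drinking is a success, yet she has no value on this outcome unless a convention supplies one. A comparison restricted to those who still drink is no longer between the groups as randomised.

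**Working it through.** **1. The plan's own figure.** The only figure nearby is the power statement: more than 99% with 1333 women, three groups, two measurements and alpha .001. Assume small means Cohen's f = 0.10 and the pre-post correlation is 0.5; the article gives neither number. Noncentrality is f² × N × m / (1 − ρ) = 0.01 × 1333 × 2 / 0.5 = 53.3 on 2 and 1330 degrees of freedom, giving power of 99.99%. It is 99.0% at ρ = 0.25 and 93.9% at ρ = 0. The claim reproduces for ρ of about 0.25 or more, and splitting .001 over two outcomes leaves 99.97% at ρ = 0.5. This test has no bearing on which outcome decides H1.

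**2. Count of primary items.** Abstract and H1: 1. Introduction (primary aim) and Outcomes: 2. Discussion: 6. The Discussion and the Introduction both speak of aims, so their conflict over the five items is like for like.

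**3. Where the ratio has no value.** Intake per occasion = drinks / occasions, which is 0/0 with no occasion. Stopping is not the only route. Eligibility admits women whose only qualifying pattern is 4 or more drinks once a month. With 12 occasions a year at random times (assumed Poisson), the chance of none in a given week is exp(−12/52) = 79%.

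**4. What the convention does to the mean.** Assume mean intake of 3 drinks per occasion, a fraction p of the arm stopping, and no change in anyone else. If s is the former mean intake of those who stop:

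- mean among remaining drinkers = (3 − p·s) / (1 − p)
- mean with stoppers scored 0 = 3 − p·s

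*Model A:* gamma distribution (shape 2, scale 1.5, SD 2.12), chance of stopping proportional to exp(−x/2). Then s = 3/1.75 = 1.71.
- p = 5%: (3 − 0.086)/0.95 = 3.07 among drinkers; 2.91 with zeros.
- p = 10%: (3 − 0.171)/0.90 = 3.14 among drinkers; 2.83 with zeros.

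*Model B, worst case:* lognormal distribution (SD 2, log-scale σ = √ln(1 + 4/9) = 0.606), exactly the lightest p stop. Then p·s = 3 × Φ(z_p − σ), which is 0.037 at 5% and 0.089 at 10%.
- p = 5%: 2.963/0.95 = 3.12 among drinkers; 2.96 with zeros.
- p = 10%: 2.911/0.90 = 3.23 among drinkers; 2.91 with zeros.

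Among drinkers only, the mean rises by 0.07 to 0.23 drinks, or 0.07/2.12 = 0.03 SD to 0.23/2 = 0.12 SD. With zeros it falls by 0.04 to 0.17. The drinkers-only mean rises whenever s is below 3, that is, whenever those who stop were lighter drinkers than average.

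**5. False-positive chance for H1.** H1 is one contrast, intervention against the pre-post control. Suppose either of two outcomes suffices, each at an unadjusted two-sided 5%. With independent tests the chance is 1 − 0.95² = 9.75%. With test statistics correlated at 0.7 it is 1 − P(|Z₁| < 1.96 and |Z₂| < 1.96) = 8.3%. At .001 it would be 1 − 0.999² = 0.2%.

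**The case against.** Much of the gap between one outcome and two can be read as shorthand. Where the article specifies components, in the Introduction and in Outcomes, it gives the same two; the abstract and H1 may simply use the umbrella term. The Discussion passage speaks of an aim, not an outcome, so it does not create six primary outcomes. These points soften the inconsistency but do not remove it. H1 is the formal hypothesis, and the article gives no way to pass from two outcomes to its single term.

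A reader might infer that following the plan would give an effect of the wrong sign. The article does not support that. It nowhere says that abstainers are dropped, it states an intention-to-treat analysis alongside a completers-only one, and scoring stoppers 0 gives the favourable direction. The scoring rule may sit in an analysis plan that is not shown, so its absence is not the point. What stands is that a measure needing such a rule, and whose direction can turn on it, was named as a primary outcome.

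A reader might also multiply two outcomes by three group contrasts and quote 1 − 0.95⁶ = 26.5%. That is not an error rate for H1, because the other two contrasts belong to Hypothesis 3. Even 9.8% rests on assumptions: no test level is stated, and the only alpha in the article is the .001 of the power statement.

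**Conclusion.** The point holds in two parts. The inconsistency is in the text itself and needs no assumption: one outcome, two outcomes, and a primary aim that absorbs five secondary items, with no rule linking the two primaries to H1. The weakness of intake per occasion as a primary outcome follows from its definition. Its size is illustrative, because the article gives no mean, SD or stopping rate: about 0.03 to 0.12 SD against the intervention in a drinkers-only analysis, in a field where the article itself expects relatively small effects. The upper end is a worst case in which exactly the lightest drinkers stop. The multiplicity cost for H1 is at most about 9.8% under unadjusted 5% tests with either outcome counting, and negligible at .001. The sample size is not in question here. This should be corrected before the analysts are unblinded.

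**What to change.** - In the abstract, the Introduction (primary aim and H1) and Outcomes, name one primary outcome that matches H1: total standard drinks per week at 8 weeks, from one named instrument collected in all arms, with abstainers scored 0, intervention versus control group 1. The day-of-week question under Typical Drinking is one candidate; no new data are needed.
- Make drinking days per week and drinks per drinking day supportive outcomes. Describe the latter among drinkers only, and do not use it to decide H1.
- If the sponsor keeps both components as primary, apply Holm across the two for H1 and fix one value for women with no occasion. Holm alone does not deal with the undefined ratio.
- Reword the Discussion so that the Hypothesis 2 outcomes are secondary.

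**Cost.** The two components lose separate primary status, and the registry entry must be brought into line with a dated change. Keeping both carries a power cost at Holm's first step: for a standardised difference of 0.2 at follow-up with 444 women per arm (1333/3, no baseline adjustment, both assumed), power per outcome falls from 84.6% at 5% to 77.0% at 2.5%.

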### Measures

The following measures will be used, administered at baseline, EMA, and follow-up.

#### Baseline Survey: Demographic Questions

The baseline survey will assess a series of demographic characteristics, including educational level, country of birth, marital status, income, whether the participating women have children, the number of dependent children living in the household, employment status, as well as smoking status and frequency.

#### Alcohol-Related Measures

##### Typical Drinking (Baseline and Follow-up)

Participants will also be asked to report on how much they typically drink each day of the week (eg, “How many drinks containing alcohol do you consume on a typical Monday?”)

##### Frequency of Risky Single-Occasion Drinking (Baseline and Follow-up)

Frequency of binge drinking will be assessed by asking participants how often they have had 4 or more standard drinks (containing 10 grams of pure ethanol) on 1 drinking occasion over the last 12 months.

##### Daily Alcohol Consumption (Baseline, EMA, and Follow-up)

Participants’ daily alcohol consumption will be measured using a drinking diary, where twice a week they will retrospectively report on the number of beverages they consumed each day (eg, “Thinking back over the last three days, how many standard drinks containing alcohol did you have on each day of the week?”)

##### Alcohol-Related Harm (Baseline and Follow-up)

A total of 15 items from the Rutgers Alcohol Problem Index [19] and the Young Adult Alcohol Consequences Questionnaire [20] were selected based on their age-appropriateness to our target group. Participants will be asked the following: “How many times has this happened to you while you were drinking or because of your drinking during the last year?”: “Got into fights with other people,” “Went to work drunk,” “Missed out on other things because you spent too much money on alcohol,” “Caused shame or embarrassment to someone,” “Neglected your responsibilities,” “Friends or relatives avoided you,” “Felt that you needed more alcohol than you used to in order to get the same effect,” “Tried to control your drinking (tried to drink only at certain times of the day or in certain places, that is, tried to change your pattern of drinking),” “Had withdrawal symptoms, that is, felt sick because you stopped or cut down on drinking,” “Noticed a change in your personality,” “Felt that you had a problem with alcohol,” “Missed a day (or part of a day) of work,” and “Kept drinking when you promised yourself not to,” with four possible answer categories ranging from 0 (none) to 3 (more than 5 times).

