We hypothesize that by the end of the intervention period, participants in the web-based intervention group will display significant increases in their awareness of harms associated with alcohol consumption (H2a), their motivation to reduce their alcohol consumption (H2b), social support (H2c), and current health status (H2d); they will also display significant decreases in alcohol-related harm (H2e) when compared to the pre-post control only group.

### Hypothesis 3

We hypothesize that by the end of the intervention period, participants in the control group with weekly assessment will have greater reductions in alcohol consumption compared with participants in the pre-post control group (H3a). We further hypothesize that participants in the intervention group will report a greater reduction in alcohol consumption compared with participants in the control group with weekly assessment.

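### The alcohol-related harm measure for H2e includes attempts to control drinking, which the intervention itself prompts; if items are totalled this can dilute, cancel or reverse the effect. The item count (15 stated, 13 listed) also needs reconciling.

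*Protocol article*

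**What the plan says.** In the protocol article, the section Alcohol-Related Harm (Baseline and Follow-up) announces "A total of 15 items from the Rutgers Alcohol Problem Index" and a second published questionnaire, chosen by the authors for age-appropriateness. One of the listed items is "Tried to control your drinking (tried to drink only at certain times of the day or in certain places", with a gloss that it means having attempted to alter one's drinking pattern. Every item is coded 0 to 3 by frequency over the past year, 3 meaning over five times. No reversal or separate handling is stated for any item.

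Hypothesis 2 says of the intervention group that "they will also display significant decreases in alcohol-related harm (H2e) when compared to the pre-post control only group". The same hypothesis expects motivation to cut down to rise (H2b).

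The section The Integrated Behavioral Model has intervention participants receive feedback on their consumption, set goals "around their intentions to reduce their alcohol use over the period of the intervention", and track their drinking. Under Comparator, control group 1, which is the H2e reference group, hears nothing from the study until the 8-week questionnaire.

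**The concern.** A woman who sets a goal to drink less and monitors herself against it is trying to change her drinking pattern. The harm measure counts that attempt as harm. The prompt to make it is given to the intervention group and not to control group 1, so the distortion differs by arm. The better H2b succeeds, the more this item pulls against H2e.

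The risk is that a real reduction in harm is missed, or that the intervention appears to raise harm when participants are doing what it asks of them.

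**Working it through.** **Step 1: item count.** Stated: 15. Listed after "Participants will be asked the following: “How many times has this happened to you while you were drinking or because of your drinking": fights; drunk at work; missing out through spending; shame; neglected responsibilities; avoidance by others; tolerance; control attempts; withdrawal; personality change; problem recognition; missed work; broken promise to oneself. That makes 13, so the stated figure is not reproduced. The list closes with a conjunction before its last entry and is not marked as a set of examples, unlike the sample questions under Typical Drinking and Daily Alcohol Consumption. For a simple sum, the maximum is 13 x 3 = 39 or 15 x 3 = 45.

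**Step 2: weight of the control-attempt item.** The article states no scoring rule, so a simple sum is an assumption. The item carries 3/39 = 7.7% of the range with 13 items, or 3/45 = 6.7% with 15.

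**Step 3: effect on the total.** Let *a* be the rise on the control-attempt item and *b* the fall on each of the other items, both as intervention minus control group 1. With 13 items the net change is *a* - 12*b*; without the control-attempt item it is -12*b*. With 15 items, 14 replaces 12. All values of *a* and *b* are assumed. For scale, *a* = 0.3 is 30% of women moving up one code (0.30 x 1) or 10% moving up three (0.10 x 3).

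| *a* | *b* | Net, 13 items | Without the item | Net, 15 items | Without the item |
|---|---|---|---|---|---|
| 0.3 | 0.02 | +0.06 | -0.24 | +0.02 | -0.28 |
| 0.3 | 0.05 | -0.30 | -0.60 | -0.40 | -0.70 |
| 0.3 | 0.10 | -0.90 | -1.20 | -1.10 | -1.40 |
| 0.6 | 0.02 | +0.36 | -0.24 | +0.32 | -0.28 |
| 0.6 | 0.05 | 0.00 | -0.60 | -0.10 | -0.70 |
| 0.6 | 0.10 | -0.60 | -1.20 | -0.80 | -1.40 |
| 1.0 | 0.02 | +0.76 | -0.24 | +0.72 | -0.28 |
| 1.0 | 0.05 | +0.40 | -0.60 | +0.30 | -0.70 |
| 1.0 | 0.10 | -0.20 | -1.20 | -0.40 | -1.40 |

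The benefit is cancelled when *a* = 12*b* (or 14*b*) and reversed above that. Depending on the shifts, the item dilutes, cancels or reverses the effect.

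**Step 4: recall window.** The items look back one year and follow-up is at 8 weeks, so about 52 - 8 = 44 of the 52 recalled weeks (85%) precede randomization. Genuine harm items can fall only through the remaining 8 weeks, so *b* is probably small. New control attempts within those 8 weeks can still move a woman from 0 to 3 on the contested item.

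**The case against.** The strongest reply is that the article gives items and response codes but no scoring rule, and an article may leave that to the full protocol or analysis plan. This stands, and the point is therefore conditional on the items being combined. What the article does fix is that the item is classed as harm and that harm is predicted to fall.

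A second reply is that the items come from published instruments. That carries less weight, because the authors selected a subset from two scales, so the composite is their own to define.

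Several stronger readings are tempting, and the documents do not support them:

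- **That success as a whole is scored as harm.** Most of the listed items point the intended way. The score is not inverted.
- **That an engaged participant must score higher on the control-attempt item.** A woman who already made more than five attempts in the year before baseline is at the ceiling, and no baseline distribution is given. A rise is likely, not certain.
- **That "Felt that you had a problem with alcohol" is biased in the same way.** Awareness-raising may increase it, but drinking less may lower it. Its direction is uncertain.
- **That "Kept drinking when you promised yourself not to" should also be removed.** Controls can make private promises, and failed control is plausibly real harm that an effective intervention should reduce.
- **That the withdrawal item, "felt sick because you stopped or cut down on drinking", belongs with them.** The link is only indirect, and the intervention is not designed to produce such symptoms.

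The item-count mismatch may simply be two items omitted from the article. It is a separate, minor matter and adds nothing to the bias argument.

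**Conclusion.** The concern holds for one item. Classing attempts to control drinking as harm conflicts with an intervention that prompts such attempts and a hypothesis that predicts less harm. If the items are totalled as written, H2e is biased against the intervention, and randomization does not remove this.

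The size cannot be estimated from the document. In the illustrations the result runs from mild dilution (-0.90 instead of -1.20) through cancellation to reversal. These rest on an assumed simple sum and assumed item shifts, and they cannot be put on a standardized scale without a standard deviation.

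The consequence is limited. Alcohol-related harm is a secondary outcome, the primary result is unaffected, and the bias would not create a false claim of benefit. It could produce a false null or an apparent increase in harm. The mismatch of 15 stated against 13 listed is confirmed as a reporting inconsistency that leaves the score range open.

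**What to change.** Before the analysts are unblinded:

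1. Define the H2e harm score without the control-attempt item, and report that item separately as a measure of change effort.
2. Present the full item set as a sensitivity analysis.
3. Add a further sensitivity analysis that also leaves out the problem-recognition item.
4. Keep the broken-promise item in the score.
5. Reconcile 15 with 13, list any missing items, check whether they too describe change effort, and state the range. For a simple sum, the full set runs to 39 or 45. Without the control-attempt item it runs to 12 x 3 = 36 or 14 x 3 = 42.

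This changes only the scoring rule and needs no new data. The cost is one item fewer in the main score, with slightly lower reliability, and two sensitivity analyses.
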